### Longitudinal Follow-Up:

Participants who completed Part A of the study will be asked to complete online questionnaires every six months for up to two years following the intervention. If they agreed to the collection of academic information in Consent A, a member of the study team will work with the local college/university to obtain this information. Participants will be mailed \$10 in the form of a check for each online follow-up assessment they complete. The assessment will be the same as the initial survey battery. A member of the study team will review the participants' scores for potential safety concerns within 24 hours following a survey submission.

If a participant indicates mild suicidal ideation (BDI #9 Suicide Item = 1, which is endorsed by 10-15% of the college student population nationwide) and moderate depressive symptoms (BDI total score = 19-29), [name], the PI of the study, will be notified, and a member of the study team will reach out to that participant via phone and/or email in order to provide an assessment via phone or in person. See below \* for potential outcomes and actions that may follow this assessment. At minimum, the study team member will provide the student with a list of mental health resources and discuss with the participant a plan in case their symptoms worsen.

In the event the student endorses 2 or higher on the BDI #9 Suicide Item (indicating suicidal ideation with intent) or a 1 on the BDI #9 item and severe depressive symptoms (BDI total score > 29), [name], the PI of the study, will be notified, and a member of the clinical study team will contact the student via phone and/or email in order to provide an assessment via phone or in person. In the event that the student does not respond, the University will be informed about the scores of the student and may contact them.

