\* In accordance with clinical practice, if the study clinician determines there is clinically significant suicidality on further evaluation, they will recommend appropriate steps. This may range from contacting other treaters, if any; arranging for an urgent appointment at the University or College counseling program; or referring the student to a local emergency service such as the Acute Psychiatry Service at MGH. Depending on the nature/level of the risk and the student's ability to comply with recommendations, the study clinician may also need to issue a Section 12 that authorizes emergency transport to and evaluation in an appropriate facility. Study participants will be informed of the risks associated with study participation including the possibility that in the event that there is concern about a serious risk of suicidality (or harm to others), participants' private information may need to be shared in order to ensure his or her safety. These procedures are clearly described in the consent forms.

For academic information, participants must sign a separate section of Consent form B. This is asking for permission to obtain, in collaboration with each university, academic information for the participants. All information obtained through the school registrar and counseling center. The following measures will be obtained via the college of enrollment every 12 months for those who have given written permission.

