## PROTOCOL SUMMARY

six months for two years following the screening. The online follow-up assessments will begin within two months after the completion of the RT intervention. These self-report measures will be collected using REDCap (Research Electronic Data Capture), a platform for electronic data capture that streamlines data collection and management, and ensures data integrity, resulting in improved data quality. The REDCap software allows researchers to design and implement study surveys for collecting, storing, retrieving, and manipulating data electronically. Participants will enter survey responses into electronic assessment forms, and the responses are then transmitted securely via encrypted connection and stored in a secured database. This electronic data capture eliminates the need for subsequent data entry by staff, thus minimizing human error. For this study, participants will complete the electronic assessments on their own computer terminals, under specific usernames sent by the Research Assistant in individually addressed e-mails. Using 128 bit RSA Secure Socket Layer (SSL) encryption, pre-determined users will log in to the questionnaires using secured browsers behind the MGB Healthcare Systems IS corporate firewall. Participants will be e-mailed a unique identifying key that will link them to various electronic forms. Therefore, each student/subject will only have access to his or her own survey data.

Data will be stored automatically and securely on an MS SQL Server, accessed over industry standard SSL 128 bit RSA encryption during data transfers. Data is routinely backed up locally onto a redundancy server and stored in a separate database. Long term storage on MGB servers occurs nightly and allows for incremental backup over multiple systems. Therefore, should one drive be physically damaged, there will be multiples within the chain to replace it. Both data servers are stored within MGB IS corporate firewall, in a secure, key access facility with password-protected computers. Only vetted MGB IS security officials will have access to physical machines storing study data. Since data are stored on a protected server, a compromise of any individual computer at a research facility will not lead to a breach of the secure database. Individual computers designated for data capture do not store participants' identifying information or study data.

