### **6) Biostatistical Analysis**

To measure the feasibility and acceptability of the prevention program (Aim 1), we will conduct qualitative and quantitative analyses of the recruitment and retention of participants to the RT Intervention. We will report descriptive statistics of those who participated in the RT group and compare them to those who were offered the group and declined. In addition, we will conduct analyses of the knowledge, feasibility, and acceptability measures to determine whether the RT Intervention increased participant's knowledge base of resilience-promoting tools and behaviors. To measure the efficacy of the program (Aim 2), we will conduct repeated measures analysis of variance (ANOVAs) to determine whether the RT Intervention leads to improvement of symptoms (i.e., psychotic experiences, depression and anxiety, the primary outcomes), social functioning/processing, and resilience, compared to the WLC condition. In addition, we will utilize linear and logistic regression to examine potential moderators to treatment response. To measure the impact of the program on long-term outcomes (Aim 3) we will conduct linear regressions using a dichotomous responder variable to regress on the psychological, social, and school functioning variables over time. Further exploratory longitudinal analysis will be conducted with hierarchical linear regression (HLM) to examine person-level variables that may impact long-term outcomes. Finally, multiple regression analyses will be conducted to identify predictors of symptom change and long-term outcomes (Aim 4).

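### Aim 3 names linear regression as its main analysis of outcomes measured repeatedly on the same students and keeps the repeated-measures model (HLM) for exploratory work; if waves are pooled, standard errors for student-level differences are too small.

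*Protocol*

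**What the plan says.** Protocol Section 6 (Biostatistical Analysis) gives the Aim 3 method in one sentence: "we will conduct linear regressions using a dichotomous responder variable to regress on the psychological, social, and school functioning variables over time". The next sentence adds: "Further exploratory longitudinal analysis will be conducted with hierarchical linear regression (HLM) to examine person-level variables that may impact long-term outcomes". For the short-term efficacy aim (Aim 2), the same paragraph says "we will conduct repeated measures analysis of variance (ANOVAs) to determine whether the RT Intervention leads to improvement of symptoms".

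The data come from the Longitudinal Follow-Up part of Section 5. Participants are "asked to complete online questionnaires every six months for up to two years following the intervention". For GPA, use of behavioral health services and enrollment status, "The following measures will be obtained via the college of enrollment every 12 months for those who have given written permission". The REDCap subsection counts the two years from screening rather than from the intervention, and adds: "The online follow-up assessments will begin within two months after the completion of the RT intervention".

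The protocol gives no sample size, within-student correlation or significance level for Aim 3. It does not say whether the waves enter one regression together or are analysed one at a time.

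**The concern.** Scores from one student at successive waves are correlated. Linear regression with its usual standard errors treats every row as independent. If the follow-up waves are stacked, a student-level predictor such as responder status is credited with several times as many independent observations as there are students, and chance differences in long-term level are declared significant too often.

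The paragraph also allocates methods. Aim 2 gets a repeated-measures method. Aim 3, which has the longer series, gets linear regression, and HLM is assigned to exploratory work on person-level variables. A statistical analysis plan that follows the protocol would carry that allocation forward. At stake are the p-values and confidence intervals for the long-term claim, though not the primary outcomes, which the protocol tests under Aim 2.

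**Working it through.** The protocol states no Aim 3 figure to reproduce, so the check asks what pooled linear regression would do.

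**Inputs from the protocol.** Questionnaires: 24 months / 6 months = 4 waves. The number 4 is not stated, and the REDCap wording on anchor and start could make it 5. School records: 24 / 12 = 2.

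**Assumptions.** Within-student correlation ρ from 0.3 to 0.7, balanced data, two-sided 5%, large-sample normal theory. Pooling of waves is itself an assumption.

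**Level difference (student-level predictor), exchangeable correlation.** With m scores per student, true variance / naive variance = 1 + (m − 1)ρ. The actual false-positive rate is 2 × [1 − Φ(1.96 / √(1 + (m − 1)ρ))].

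| m | ρ | Variance ratio | Naive SE / true SE | False-positive rate |
|---|---|---|---|---|
| 4 | 0.3 | 1.9 | 0.73 | 15.5% |
| 4 | 0.5 | 2.5 | 0.63 | 21.5% |
| 4 | 0.7 | 3.1 | 0.57 | 26.6% |
| 2 | 0.3 | 1.3 | 0.88 | 8.6% |
| 2 | 0.5 | 1.5 | 0.82 | 11.0% |
| 2 | 0.7 | 1.7 | 0.77 | 13.3% |

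A simulation with 100 students, m = 4, ρ = 0.5 and 2,000 runs gave 21.3% for ordinary standard errors and 4.95% for cluster-robust ones.

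**Does this depend on the correlation pattern?** Under AR(1), where correlation decays with the gap between waves, the variance ratio at m = 4 is 1 + (3ρ + 2ρ² + ρ³)/2. At ρ = 0.5 this is 1 + 2.125/2 = 2.0625, and the false-positive rate is 17.2% (11.6% at ρ = 0.3, 23.4% at 0.7). With a random intercept variance of 0.5, residual variance of 0.5 and random-slope variance from 0.02 to 0.3, naive/true SE stays at about 0.63. Five waves make it worse: 18.6% to 31.5% exchangeable, 12.3% to 26.4% AR(1). The naive standard error is too small in every case tried.

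**Trend difference (predictor by wave).** Here the pattern decides the direction.

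- Exchangeable: true/naive variance = 1 − ρ, so naive/true SE is 1.20, 1.41 and 1.83 at ρ = 0.3, 0.5 and 0.7. It is too large.
- AR(1), m = 4: true/naive variance = (5 + 2.5ρ − 3ρ² − 4.5ρ³)/5. At ρ = 0.5 this is 4.9375/5 = 0.9875, so naive/true SE = 1.01. At ρ = 0.3 it is 0.97 and at ρ = 0.7 it is 1.16.
- AR(1), m = 5: 0.92, 0.91 and 1.00.
- Random slopes as above, m = 4: the ratio falls from 1.34 to 1.01 as slope variance rises from 0.02 to 0.3.

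**If waves are analysed separately.** Each regression then has one row per student and the independence problem disappears. But four tests per outcome, with test statistics correlated 0.7 to 0.3, give a 13% to 17% chance of at least one false positive (simulation), and none of them tests course over time.

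**The case against.** The strongest reply is that pooling is not in the text. The protocol says linear regressions, in the plural, and calls them neither ordinary nor stacked. One regression per outcome and wave, or on a change score or student-level slope, fits the words and breaks no independence assumption. The unit of analysis and covariance structure are usual content of a statistical analysis plan, which is not shown. The paragraph is plainly aware of repeated measures, since it names repeated measures ANOVA and HLM.

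Much of this stands. The error in level differences is conditional on pooling, and silence on covariance structure would not be a finding. What remains is that the protocol does name a method for each aim, puts the suitable one for Aim 3 under exploratory work, and nowhere limits Aim 3 to one score per student.

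A reader might also infer that pooled regression must make trend standard errors too large, so that Aim 3 would be wrong in both directions. The documents do not support that. It follows under exchangeable correlation, but the protocol gives no correlation pattern, and decaying correlation or sizeable random slopes brings the trend standard error close to right or slightly below.

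Two further limits stand. The sentence leaves unclear whether responder status is predictor or outcome, and the calculation takes it as predictor. Follow-up runs for up to two years, so students who complete fewer waves would lower the four-wave figures.

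**Conclusion.** The point holds in conditional form. The protocol's main Aim 3 method makes no stated allowance for repeated scores on the same student, and the named model that would do so is confined to exploratory use. If waves are pooled, false-positive rates for student-level differences rise from 5% to roughly 15% to 27% (four waves) or 9% to 13% (two yearly records), assuming exchangeable correlation of 0.3 to 0.7 and complete follow-up. The direction, standard errors too small, held under every positive correlation pattern tried. The size cannot be taken from the protocol. No general direction can be claimed for trend differences. This should be corrected, but it concerns a long-term aim and leaves the primary-outcome analysis untouched.

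**What to change.** In Section 6, make the HLM already named the main Aim 3 model rather than an exploratory addition:

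- The functioning score is the outcome, with one row per student per wave.
- Fixed effects are wave, predictor and predictor-by-wave.
- Within-student covariance is unstructured, or the model has a random intercept and slope, or cluster-robust standard errors are used. A random intercept alone is not enough, because it imposes the exchangeable pattern and would understate the standard error of predictor-by-wave if students' slopes differ.
- Yearly yes/no school records use GEE or a logistic mixed model.

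Alternatively, if one score per student was meant, state that each regression uses one pre-specified wave or summary score, and name it.

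The cost is a few sentences in Section 6, slightly more analysis work and wider intervals for level differences. No new data, visits or participants are needed.

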## PROTOCOL SUMMARY

Students may also be contacted if their screening questionnaires are missing important information, as long as they indicate that they are willing to be re-contacted in the consent form.

During the screening event, if eligible, students will be assessed for their interest in Part B (the RT intervention) portion of the study. Also, all students who participate in Part A will be offered a list of local mental health resources in the event that they wish to seek treatment outside of the study procedures. All students will be given a \$20 gift card for their participation in the screening.

The following measures will be included in the assessment battery:

1. Demographic information
2. Family psychological health history measure
3. Self-report psychological health history measure
4. *Beck Depression Inventory (BDI)*, a 21-item questionnaire for the assessment of degree of depression\*
5. *21-Item Peters et al. Delusions Inventory (PDI-short version)*, a 21-item questionnaire for the psychometric measurement of schizotypal traits and symptoms\*
6. *State-Trait Anxiety Inventory (STAI)*, a 40-item questionnaire for the assessment of anxiety levels\*
7. *Positive and Negative Affect Schedule (PANAS)*, a 20-item questionnaire for assessing positive and negative affect.
8. *Launay-Slade Hallucination Scale (LSHS)*, a 16-item questionnaire used to assess hallucinatory thoughts
9. *Childhood Trauma Questionnaire (CTQ-M)* a 47-item questionnaire for the assessment of childhood trauma
10. An adapted version of the “*Monitoring the Future*” *Substance Use Scale (MTF-2)* a survey asking detailed questions about subjects’ use of 12 categories of substances.
11. *Perceived Stress Scale (PSS)*, a 10-item, widely-used psychological instrument for measuring the perception of stress.
12. *Interpersonal Reactivity Index (IRI)*, a 28-item questionnaire for assessing multiple dimensions of empathy.
13. *Social Network Index Adapted for College Students (SNI-adapted)*, a 12-item questionnaire used to assess the size and diversity of an individual’s social network.
14. *Chapman Social Anhedonia Scale revised (SAS)*, a set of 40 true-false questions used to assess the level of pleasure experienced from and importance assigned to social interaction.
15. *Time Alone Questionnaire (TAQ)*, a 6-item questionnaire used to assess the portion of waking hours spent with others, compared to desired amount of time spent with others.

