16. *Psychological Well-Being Midus-1 Version (PWB)*, an 18-item questionnaire for assessing several qualities of overall well-being.
17. *UCLA Loneliness Scale*, a 20-item scale to measure one’s subjective feelings of loneliness.
18. *Self-Compassion Scale (SCS)*, a 26-item scale for the assessment of self-compassion.
19. *General Self-Efficacy Scale (GSE)*, a 10-item questionnaire for the assessment of self-efficacy, the ability to cope with stressors.
20. *Five Facet Mindfulness Questionnaire (FFMQ)*, a 39-item questionnaire that assesses the 5 domains of mindfulness.
21. *Connor-Davidson Resilience Scale (CD-RISC)*, a 25-item questionnaire for assessing resilience.
22. *Aberrant Salience Test (AbSal)*: a list of 108 words to be rated as neutral or negative, designed to measure negative attribution bias.
23. *Paranoia Checklist – 5-item (PC-5)*: a 5-item measure of symptoms of paranoia.
24. *Mentalization Scale (MentS)*, a 28-item questionnaire to assess mentalization.

\*primary outcomes, predicted to decrease in magnitude following RT but not following the WLC condition.

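### Aim 3 is planned on a yes/no responder variable although the symptom outcomes are multi-item scores; continuous change would keep information that the cut discards

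*Protocol*

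**What the plan says.** Section 6 (Biostatistical Analysis) sets the Aim 3 method in one sentence: "we will conduct linear regressions using a dichotomous responder variable to regress on the psychological, social, and school functioning variables over time". A hierarchical linear model follows, labelled exploratory, so the regression with the responder variable is the named analysis for this aim.

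The same section calls "psychotic experiences, depression and anxiety, the primary outcomes" and tests them under Aim 2 by repeated measures ANOVA. Aim 4 uses multiple regression on symptom change and long-term outcomes. Neither states a cut.

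The assessment battery in Section 5, Part A, marks three instruments with an asterisk: the BDI, "a 21-item questionnaire for the assessment of degree of depression"; the PDI, "a 21-item questionnaire for the psychometric measurement of schizotypal traits and symptoms"; and the STAI, "a 40-item questionnaire for the assessment of anxiety levels". The footnote describes them as "primary outcomes, predicted to decrease in magnitude following RT but not following the WLC condition".

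**The concern.** The trial's hypothesis is graded: scores should go down. A responder variable keeps only which side of a line a student falls on. Students just either side of the line count as different, and all students on one side count as the same. The protocol gives no clinical, regulatory or practical reason for doing this in Aim 3.

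At stake is the chance of finding a real relation between short-term symptom change and later psychological, social and school functioning. That relation is studied with six-monthly questionnaires for up to two years, so losing information at the analysis stage is a poor return on the follow-up.

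**Working it through.** **Nothing to reproduce.** The protocol states no sample size, effect size, alpha, power or responder share.

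**From the protocol:** the responder variable in Aim 3, the three multi-item primary scales and the predicted decrease (Sections 5 and 6).

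**Assumed:** response is judged on those scales, which Section 6 does not spell out; change is roughly normal; alpha is 5% two-sided; the continuous analysis has 80% power (50% to 95% also shown); the responder share is 20% to 50%.

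**Step 1, information kept.** When a normal variable is cut so that a share p responds, its relative efficiency is E = φ(z_p)² / [p(1 − p)].
- p = 0.5: φ(0) = 0.3989, so E = 0.1592 / 0.25 = 0.637.
- p = 0.2: φ(0.8416) = 0.2800, so E = 0.0784 / 0.16 = 0.490.

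**Step 2, power after the cut.** Power = Φ[(1.960 + z_power) × √E − 1.960]. With 80% power the bracket starts from 1.960 + 0.842 = 2.802.
- p = 0.5: 2.802 × 0.798 − 1.960 = 0.275, so power is 60.8%.
- p = 0.2: 2.802 × 0.700 − 1.960 = 0.001, so power is 50.0%.

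| Responder share | Information lost | Power, from 80% | Points lost | Sample multiple for equal power (1/E) |
|---|---|---|---|---|
| 50% | 36.3% | 60.8% | 19.2 | 1.57 |
| 40% | 37.8% | 59.8% | 20.2 | 1.61 |
| 30% | 42.4% | 56.6% | 23.4 | 1.74 |
| 20% | 51.0% | 50.0% | 30.0 | 2.04 |

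**Step 3, other base powers at a 50% share.**

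| Continuous power | After the cut | Points lost |
|---|---|---|
| 50% | 34.6% | 15.4 |
| 60% | 42.3% | 17.7 |
| 70% | 50.9% | 19.1 |
| 80% | 60.8% | 19.2 |
| 90% | 73.4% | 16.6 |
| 95% | 82.0% | 13.0 |

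The loss at this share peaks at 19.4 points, at a base power of about 75%.

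**Step 4, predictor or outcome.** The Aim 3 sentence leaves unclear which side of the regression the responder variable sits on, so both were checked.
- *As predictor:* simulation with 4,000 runs per case and correlations of 0.2, 0.3 and 0.5 (n = 194, 85 and 29, about 80% power uncut) gave losses of 20 to 21 points at a 50% share and 31 to 35 points at 20%.
- *As outcome:* a two-group comparison with standardised differences of 0.3, 0.5 and 0.8 (175, 63 and 25 per arm, about 80% power uncut) left 53% to 61% power after a cut with 20% to 50% responders in the reference group.

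The cost is similar either way.

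**Step 5, dependence on shape.** For a uniform change score cut at the median, E = (0.25 / 0.2887)² = 0.75, a 25% loss. For a Laplace score cut at the median, E = 0.50, a 50% loss. The 36% figure is therefore a minimum for normal change only.

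**The case against.** The strongest reply is that the reach is small and every figure is conditional. Aim 2, which tests the primary outcomes, has no stated cut; Aim 4 models symptom change directly; and Aim 3 also has an exploratory hierarchical model. This stands as a limit on the point, but none of these replaces the analysis named for Aim 3.

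A second reply concerns multiplicity. If one overall responder variable was intended, replacing it with three scales means three tests. With a Bonferroni correction over three (critical value 2.394), an 80% test has power Φ(2.802 − 2.394) = 66%, against 61% for a single responder variable at a 50% share. Most of the gain would disappear in that case. This stands, and the fix has to deal with it.

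Three stronger readings are tempting, and the documents do not support them.
- *The moderator models also discard the information.* A reader might infer this from the word logistic. The text, however, says "we will utilize linear and logistic regression to examine potential moderators to treatment response", so linear models are already planned there, and a cut version of the symptom scales is nowhere stated.
- *Most students can change by only a few points, so a cut is especially harmful.* Section 3 sets lower bounds only (PDI at least 4, BDI at least 6), and Section 2 describes mild-to-moderate severity. Nothing confines change to a few points.
- *The cut-off is missing.* A responder definition, and a reason for it, may sit in a statistical analysis plan that is not shown. A definition would not restore the discarded information, and the point does not depend on its absence.

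**Conclusion.** The point holds for Aim 3 only. The protocol itself chooses a yes/no variable for this aim, gives no reason, and has scores on which the full change could be used. Under the assumptions listed above, the loss is about 19 to 30 points of power from a base of 80% with 20% to 50% responding.

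A reader might take 20 points as a minimum loss. It is not: at a 50% share the loss stays below 20 points at every base power. Nor is a third of the information a universal minimum, since the loss depends on the shape of the change distribution.

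This is an inexpensive improvement to a stated aim, and no primary efficacy conclusion depends on it.

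**What to change.** In the Aim 3 sentence of Section 6, replace the responder variable with continuous symptom change: enter the post-intervention score with the baseline score as covariate, and say plainly that it is the predictor of later functioning. To avoid trading the gain for extra tests, name one scale or a prespecified composite as the main Aim 3 predictor, or treat the three scales as a family with a stated correction. Keep responder percentages as a supportive description.

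The cost is a short edit to Section 6. The scores are already collected before and after the intervention, so no new data, visits or participants are needed. A slope per scale point is less simple to describe than responder versus non-responder, which the descriptive percentages partly offset. Choosing a main scale or composite also needs a decision that the present wording avoids.

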## PROTOCOL SUMMARY

**Aim 2:** To measure the efficacy of the program in inducing short-term improvements in basic social processes (theory-of-mind capacity, personal space behaviors), social functioning (level of social activity, social satisfaction), resilience factors (ability to handle stress, self-efficacy) and symptom levels (attenuated psychotic symptoms, depression, and anxiety).

**Aim 3:** To measure the impact of the program on long-term outcomes (psychological, social, and school functioning).

**Aim 4:** To assess whether certain subject characteristics at baseline predict short-term and long-term outcomes.

The study includes 2 parts (each of which has a separate consent form):

Part A: A screening for eligible participants

Part B: The RT intervention

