Control Group: After an initial piloting phase of the intervention, a waitlist control (WLC) group will be added to the study design. Half of the enrolled students (randomly selected during the pre-workshop/baseline assessment) will be selected for Group 1, which starts immediately following session B1, while the other half (Group 2) asked to wait for one round (approximately 4 weeks) before starting the RT intervention. The WLC students will complete the initial assessments at the same time as the students who will receive the RT intervention immediately and will also complete assessments before and after the 4-week intervention they complete. Thus, the WLC participants will undergo three assessments following the screening, rather than the two assessments (before and after the intervention) that the first group of students will complete. Although exclusionary criteria for Part B include current enrollment in psychological or behavioral health treatment, students in the WLC group will not be dissuaded from seeking treatment during the waitlist period, and eligibility for Part B will be reassessed prior to their enrollment in the intervention.

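### Aim 3 asks for the program's long-term impact, but its main analysis compares responders with non-responders, which is a prognostic contrast with no randomised control behind it

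*Protocol*

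**What the plan says.** The Specific Aims in the protocol word Aim 3 as a question of effect: "To measure the impact of the program on long-term outcomes (psychological, social, and school functioning". Section 6 (Biostatistical Analysis) gives its main analysis: "we will conduct linear regressions using a dichotomous responder variable to regress on the psychological, social, and school functioning variables over time". The responder variable is not defined, and neither study arm nor any unexposed group appears in that sentence. For Aim 2, the same section does name a comparator: outcomes are "compared to the WLC condition".

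The control is described in section 4 (Subject Enrollment, Control Group). Allocation is by halves: "Half of the enrolled students (randomly selected during the pre-workshop/baseline assessment) will be selected for Group 1", "while the other half (Group 2) asked to wait for one round (approximately 4 weeks) before starting the RT intervention". The waitlist is added only after a pilot phase, and waitlist students are re-checked for eligibility before they enter RT.

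Section 5 asks everyone who completed Part A for online questionnaires every six months for up to two years (Longitudinal Follow-Up). The REDCap paragraph says these begin within two months after RT is completed.

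**The concern.** An impact question needs a contrast between having the program and not having it. Responder versus non-responder sorts students by how they fared over the first weeks. Any stable difference between students that affects both the early change and the later score enters that contrast, whether or not RT works.

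The design does not supply the missing comparator. By the time long-term follow-up starts, the randomised control group has been scheduled for RT as well. If section 6 is followed as written, a difference in prognosis would be reported as the program's long-term effect.

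**Working it through.** **1. No figure to reproduce.** The protocol gives no sample size, power, alpha or effect size for this aim. The check sets the passages against each other and then asks what the regression returns when RT has no effect.

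**2. Timeline.**
- Control group: "asked to wait for one round (approximately 4 weeks) before starting the RT intervention" (section 4).
- Long-term questionnaires: start after RT is completed, then six-monthly for up to two years (section 5).
- Result: the randomised contrast of RT with no RT lasts about 4 weeks and has ended before the first long-term wave. Pilot-phase students never had a concurrent control.

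Replacing responder status by randomised arm would remove the bias but would not answer Aim 3. For illustration, with an assumed true effect of 0.5 SD and 50 students per arm, power is 71% if the control stays untreated. Once both arms share the same lasting effect, the expected long-term difference is 0 and power falls to alpha.

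**3. Why the contrast need not be zero under the null.** Let B be the B1 score, P the post-RT score and L a later score. Take a common variance s², a common correlation r and no RT effect. Then:
- Cov(L, P | B) = s²(r - r²) = s² r(1 - r).
- This is 0.24 s² at r = 0.6, 0.21 s² at r = 0.7 and 0.16 s² at r = 0.8, positive whenever r lies between 0 and 1.
- Given B, being a responder means having a low P, and a low P goes with a low L. A baseline-adjusted regression therefore favours responders although RT does nothing.
- Without adjustment, Cov(L, B - P) = s²(r - r) = 0, so nothing fixes the sign. It depends on the responder rule and the shape of the scores.

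**4. Size under the null.** Input from the protocol: BDI entry cut-off of 6 (section 3), with the BDI measured again at B1 (section 5, Pre-Workshop/Baseline Session). Assumptions not in the protocol: right-skewed BDI, mean 9, SD 7.5; retest correlation 0.6 to 0.8; entry on the screening BDI only; no RT effect. The difference is responders minus non-responders in later BDI, in SD units; negative means responders look better.

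| Responder rule (B1 to post-RT) | Unadjusted difference |
|---|---|
| Fall of at least 50% | -0.20 to -0.36 |
| Fall of at least 5 points | +0.24 to +0.36 |
| Fall of at least 3 points | +0.14 to +0.20 |

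At SD 7.5 the first row is 0.20 × 7.5 = 1.5 to 0.36 × 7.5 = 2.7 BDI points. With the B1 score in the model, responders look better by about 0.3 to 0.55 SD under every rule tried. A rerun with gamma-shaped scores (shape (9/7.5)² = 1.44, scale 7.5²/9 = 6.25) gave the same ranges to within about 0.02.

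**5. Sensitivity to the model.** A second null model used normal scores (mean 9, SD 7), 100 students and correlations of 0.4 to 0.7, with entry selected on the same baseline that defines change. Responders looked better in all 27 combinations of rule, outcome form and correlation, by 0.20 to 0.82 SD. A significant false benefit appeared in 16% to 94% of simulated trials, against 2.5% expected in that direction. With uncorrelated scores, the unadjusted and baseline-adjusted forms returned to 2% to 3%. A randomised two-arm comparison under the null rejected in 5.4% of trials (two-sided, nominal 5%).

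**The case against.** The strongest reply is that the responder definition belongs in an analysis plan that is not at hand, so the direction and size of any bias are unknown. That part stands. A reader might infer that the Aim 3 regression would show a benefit even for an inert program. The protocol does not support so firm a statement: a 5-point rule without baseline adjustment reverses the sign. The uniformly favourable results in step 5 select entry on the same score that defines change, whereas the protocol measures the BDI again at B1. But no definition of responder turns the contrast into program versus no program, and the protocol itself fixes that contrast.

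Other stronger readings also fail:
- **That every student has been offered RT by then.** Ineligible students and decliners from Part A are followed too, and some waitlist students may be found ineligible on reassessment. These students are untreated but not a randomised control, and the Aim 3 sentence does not use them.
- **That repeated waves are ignored.** Section 6 adds an exploratory hierarchical linear analysis. It targets person-level variables rather than the program effect, so it does not answer Aim 3, but it does address the longitudinal structure.
- **That moderators are analysed through the same dichotomy.** The text reads "we will utilize linear and logistic regression to examine potential moderators to treatment response". Linear regression suits a continuous response, and an interaction with arm is not ruled out.
- **That a linear model is fitted to a binary outcome.** The wording can be read with responder status as the dependent variable, but this is an ambiguity and not a demonstrated error. That reading contains no program contrast either.

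**Conclusion.** The point holds as a mismatch between aim and analysis. Aim 3 asks for impact. The stated main analysis gives a non-randomised prognostic comparison, and the waitlist crossover leaves no randomised untreated group in the long-term window. This conclusion rests on the protocol text alone, together with the ordinary meaning of responder as a status set after treatment.

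The size rests on assumptions about the BDI distribution, its retest correlation and the responder rule. Under these, a null program yields unadjusted differences from -0.36 to +0.36 SD, and baseline-adjusted differences of about 0.3 to 0.55 SD in favour of responders. For GPA or enrolment status, the size would depend on how these correlate with the symptom that defines response.

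This should be fixed. It does not threaten the primary outcomes, which belong to the randomised Aim 2 comparison.

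**What to change.** In section 6, label the responder regression as prognostic or exploratory and state that it will not be reported as program impact. Say which variable is dependent. Limit causal claims to the randomised waitlist period of about 4 weeks.

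If long-term impact is still to be estimated, fit a mixed model over all follow-up waves. Compare RT recipients with Part A students who met the Part B score criteria, did not receive RT and are not known to meet the Part B exclusions. The last condition matters: without it, the comparator would include students kept out for active diagnosis, current treatment or psychotropic medication. Adjust for baseline scores and campus, and label the result observational.

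The cost is a rewording of section 6 and of Aim 3 as a non-randomised comparison, plus some analysis work; no new measures are needed. Self-selection among decliners will remain. Follow-up waves need aligning, because section 5 counts the two years from the intervention in one place and from screening in another. Part A questionnaires are also described only as ones that may be sent, so the comparator's completeness is not assured.
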